### 2.5. Interventions

#### 2.5.1. Interventions

Patients who meet the inclusion criteria and none of the exclusion criteria are randomized into one of four treatment groups: (1) high-dose group: 3 bags of SGLNG/time; (2) middle-dose group: 2 bags of SGLNG plus 1 bag of placebo granule/time; (3) low-dose group: 1 bag of SGLNG plus 2 bags of placebo granule/time; and (4) control group: 3 bags of placebo granule/time.

Each participant receives a large box and be instructed to dissolve one small box of the contents in approximately 200 mL of warm liquid and take orally after each meal, 3 times daily for 5 days. The participants are isolated from each other after enrollment and advised to take the drugs at home to avoid discussing the drugs. Participants, researchers, and outcome assessors will remain blinded to the treatment allocation throughout the study.

Throughout the study period, participants will not be permitted to use any other treatments for the common cold, including oral medications and TCM therapies such as cupping, massage, or acupuncture. Medications for concomitant diseases, such as hypertension, are allowed. The dosage, duration, and name of any concomitant medication or treatment will be recorded.

#### 2.5.2. Follow-Up and Compliance

The follow-up visits will last for 5 days after the treatment. Details of the study procedures are shown in Table 3. During the 11-day study period, a total of four visits (on the 1st, 4th, 6th, and 11th days) will be performed. After the enrollment, the investigators will contact each patient every day to obtain the details of dynamic changes in cold symptoms and remind them to attend the clinical visits on certain dates. The participants are required to collect the packages after taking the granules and bring them on the 4th and 6th days visits. The total actual dose is defined as the total number of bags that are actually used (by counting the number of consumed capsules).

### 2.6. Outcome Measurements

#### 2.6.1. General Information and Physical Examination

The demographics, family history, past history, medical history, vital signs, and physical characteristics (body temperature, respiration rate, heart rate, blood pressure, and body weight) are obtained and recorded on the 1st day (day 1). Physical examination and a review of concomitant medications are conducted on the 4th, 6th, and 11th days of the intervention.

#### 2.6.2. Safety Assessment

Safety assessments are taken on the 1st day (day 1) and the 6th day of the intervention including (1) vital signs and body weight; (2) full blood count, urine routine plus urinary sediment tests; (3) liver function tests (ALT, AST, TBIL, ALB, ALP, and *γ*-GT); (4) renal function tests (Cr, cystatin C, urinary albumin, and urinary NAG enzyme); (5) fasting blood glucose and 2-hour postprandial blood glucose; and (6) electrocardiogram.

The chronic toxicity test in rats revealed that SGLNG may raise blood sugar during the dosing period (lasted for 3 weeks) in both 15 times and 50 times the clinical daily dose groups; it is possible that long-term high-dose of SGLNG taken may cause blood sugar disorders in diabetic patients. The fasting blood glucose and 2-hour postprandial blood glucose tests are used to observe the effect of SGLNG on blood glucose during the trial as a safety index. What is more, it can also exclude participants with unknown diabetes before enrollment. Although the earlier multicenter, randomized, active controlled clinical study did not report that SGLNG can cause abnormal blood glucose in patients [22], we intended to add this criterion for safety consideration.

#### 2.6.3. Excluding Observation

Chest X-ray, urine pregnancy test (only for females), fasting blood glucose, and 2-hour postprandial blood glucose are assessed on the 1st day of the intervention.

#### 2.6.4. Compliance Assessment

The compliance of each participant is calculated from the total dose that was actually taken and the total dose required by the study protocol. The total actual dose is defined as the total number of bags that are actually used (by counting the number of consumed capsules), and the total required dose is defined as the number of bags that should be used during the 5-day treatment. Compliance is assessed on the 11th day after the intervention. The formula is as follows:(1)$$\begin{array}{c} Compliance=\frac{Total\;\;actual\;\;dose}{Total\;\;required\;\;dose}\times 100\%. \end{array}$$

#### 2.6.5. Primary Outcomes

*Duration of All Symptoms*. Duration of all symptoms is defined as the number of days from enrollment to the day that all symptoms disappear (the time from the symptom severity score above zero until 2 days of the severity score marked as zero). If symptom severity is marked above zero on the day after a single day of zero, the cold is defined as continuing. If the day marked above zero is the 11th day, this is defined as the end of the cold, but if symptoms last more than 11 days, follow-up will continue via phone call or e-mail until all symptoms are absent. The first day of medication administration is defined as the 1st day (day 1) in the study. The start of the day is defined as 6:00 a.m., and symptoms absent before 6:00 a.m. are regarded as occurring the day before.

Because all the participants in the trial have Qi-deficiency syndrome and normally present certain Qi-deficiency symptoms (fatigue, shortness of breath, and spontaneous perspiration), we define the disappearance of Qi-deficiency symptoms (symptom score = 0) (Table 2) as all the symptoms returning to the basic level present before the onset of common cold.

*The Total Score Reduction of Jackson's Scale*. Jackson's scale [27], which is specific for diagnosis and symptom severity assessment of common cold, contains 8 symptoms (sneezing, headache, malaise, chilliness, nasal discharge, nasal obstruction, sore throat, and cough) and rates as 0 = absent, 1 = mild, 2 = moderate, and 3 = severe. The symptom score will be summed on the 1st day and the 4th, 6th, and 11th days after intervention, and the score reduction will be calculated between the 1st day and the days after the intervention.

The symptom severity and score are assessed by researchers who are blind to the trial, and one participant is assessed by the same researcher consistently throughout trial. Participants will not be allowed to assess their overall illness or level of severity to avoid assessment bias.

*The Total Score Reduction of TCM Symptoms Scale*. In compliance with the severity measurement of common cold in the Guidelines for Clinical Research of New Chinese Medicine [28], symptom score of CCQDS is obtained from a four-point Likert-type symptom severity scale (Table 2), with different score criteria for main symptoms and secondary symptoms: (1) main symptoms: 0 = no symptoms; 2 = mild; 4 = moderate; 6 = severe; (2) secondary symptoms: 0 = no symptoms; 1 = mild; 2 = moderate; 3 = severe. The total score of TCM symptoms (including main and secondary symptoms) will be summed on the 1st, 4th, 6th, and 11th days, and the score reduction is defined as the scores on the 1st day minus the scores after the intervention, which will be calculated on the 4th, 6th, and 11th days.

#### 2.6.6. Secondary Outcomes

*The Duration of Every Single TCM Symptom. *The duration of every single TCM symptom is defined as the number of days from enrollment to the time when each single TCM symptom resolves or returns to the level (symptoms specific for Qi-deficiency) before the onset of the cold with no recurrence within 48 hours. The duration of each TCM symptom (including main symptoms and secondary symptoms) will be recorded.

*The Disappearing Rate of TCM Main Symptoms on the 4th and 6th Days. *The four main symptoms of CCQDS include aversion to cold, stuffy and running nose with sneezing, fatigue, and shortness of breath. The disappearing rate is measured as the percentage of disappeared symptoms (number of disappeared symptoms) on the 4th and 6th days.

*The Respective Total Score Reduction of TCM Main Symptoms and Secondary Symptoms. *The scores of TCM main symptoms evaluated for severity (Table 2) will be summed on the 1st day. The total score reduction of TCM main symptoms is defined as the score on the 1st day before intervention minus the scores after the intervention, which will be calculated on the 4th, 6th, and 11th day. Similarly, the total score reduction of TCM secondary symptoms will be calculated on the 4th, 6th, and 11th day by recording the score on the 1st day before intervention minus the scores after the intervention.

*Curative Effect*. The curative effect is calculated as the percentage of cumulative symptom score reduction (PSSR) recorded on the 11th day and categorized into two grades as effective (PSSR ≥ 50%) or invalid (PSSR < 50%). According to Jackson's scale and TCM symptom scale, the curative effect will be recorded, respectively. The formula is as follows: PSSR = (symptom score before treatment − symptom score after treatment)/symptom score before treatment × 100%.

*Comparison between Jackson's Scale and TCM Symptoms Scale*. Jackson's scale of common cold and TCM symptoms scale are overlapping in terms of certain symptoms, while TCM symptoms cover some other abnormal symptoms than Jackson's scale. The effect of interventions on Jackson's scale and TCM symptom scores will be compared on the 4th, 6th, and 11th days, and the consistency between the two scales will be assessed by correlation analysis.

### 2.7. Adverse Events

Participants are required to truthfully report symptom changes. Any adverse events (such as worsening of symptoms, concomitant diseases, and abnormal laboratory results) during the test will be recorded and treated appropriately by the intervention administrators until the patient's laboratory results return to normal and symptoms disappear. Follow-up will be performed via hospital visits and phone calls according to the severity of adverse event. In cases of severe adverse events, investigators are asked to record and report the events to the Drug Registration Department of the State Food and Drug Administration, the Safety Supervision Department, the Provincial Drug Supervision Bureau, the trial applicant, and the ethics committee within 24 hours.

### 2.8. Statistical Analysis

The full analysis set (FAS) is the primary analysis set for efficacy with an intention-to-treat (ITT) principle. In the FAS, all patients will be treated with at least one dose of the study drug and at least one clinical observation will be recorded in the study. All subjects without any major protocol deviations will be involved in the per-protocol set (PPS). The safety analysis will be conducted for randomized subjects who have completed at least one study visit and have safety data. Descriptive statistics will be performed on continuous variables, frequencies, and categorical variables. All symptom durations, total score reductions on Jackson's scale and TCM symptoms, the duration of each TCM symptom, the decreasing rate of TCM main symptoms, and the reduction score of TCM symptoms will be estimated with the Kaplan-Meier technique and compared using the stratified log-rank test. Comparisons among different dose groups and age layers will be conducted with an analysis of variance (ANOVA) and a least significant difference *t*-test. In this multicenter trial, the Cochran-Mantel-Haenszel test stratified by clinical centers and the logistic regression model adjusted for covariates will be used. Statistical analyses will be conducted by an independent statistician from the Health Statistics Department of the Fourth Military Medical University using the SAS statistical software 9.1.3 (SAS, Cary, North Carolina State University, North Carolina, USA).

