### 2.3. Sample Size Calculation

The sample size was determined using Encyclopaedia Medical Statistics 3.2 software (PEMS 3.2, Guangzhou Jing far Pharmaceutical Research Co., Ltd., Guangzhou, China) with 90% power and a significance level of 0.05 (two-sided). According to Lizogub et al. [30], the sample size should consist of 50 participants in each group. Considering the potential 20% loss, 60 participants are needed for each group. As there is a low-dose group, a middle-dose group, a high-dose group, and a control group with five centers involved, a total of 240 participants will be recruited in this study, with 48 patients recruited at each center.

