Secondary symptom		Fever	None	37.3–37.5°C	37.6–37.9°C	≧38.0°C
		Sore throat	None	Dry throat with slight pain	Significant with obvious pain when swallowing	Sore and swollen throat with severe pain
		Headache	None	Slight and occasionally	Severe and lasting	Severe and affect working
		Cough	None	Occasionally in daytime, not affecting daily life	Occasionally day and night, slightly affecting sleep	Frequent cough day and night, affecting rest and sleep
		Expectoration	None	Stick sputum, not easy to cough out	Stick or yellow sputum	Stick or yellow sputum with large volume
		Spontaneous perspiration	None	Yes (severe than usual)	—	—
		Tongue and pulse condition^#^	Tongue color	Pale □ Red □		Others
			Tongue coat	Thin white □ Thin yellow □		Others

^*∗*^Scores represent the severity of symptoms. ^#^The score of tongue and pulse will not be recorded.

**Table 3 tab3:** Study schedule for patients. On the 1st day, researchers collect the data of medical and treatment history, efficacy observation, safety assessment, and exclusive observation of patients, as well as randomization, allocation, and drug distribution. On the 4th day (fulfilled for 4 days to the first time of medicine consume), patients take the second visit for physical examination, and researchers record symptoms scores, combined medication, and adverse event (if any). The 6th ± 1 day (fulfilled for 6 days to the first time of medicine consume), patients take the third visit for physical examination and the second safety assessment, and researchers record symptoms scores, combined medication, adverse event (if any), and recycled medicines and pack box, and drug quantity statistics. On the 11th ± 2 day (fulfilled for 11 days to the first time of medicine consume), patients take the fourth visit for physical examination, and researchers record symptoms scores, combined medication, and adverse event (if any).

Stage	Visit period			
Treatment	Visit 1	Visit 2	Visit 3	Visit 4
Day	1 day	4th day	6th ± 1 day	11th ± 2 days

*Basic medical history recording*				
Informed consent signing	×			
General information recording	×			
Medical and treatment history recording	×			
Complication and symptoms recording	×			
Physical examining	×	×	×	×
Combined medication recording		×	×	×
*Efficacy observation *				
Symptoms scores recording	×	×	×	×
*Safety assessment *				
Routine blood test	×		×	
Routine urine + urinary sediment microscopy	×		×	
Liver function test	×		×	
Renal function test	×		×	

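### The safety set in 2.8 has no dosing condition, so a randomised patient who never took the drug could enter its denominators; the effect is probably small and cheap to remove

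*Protocol article*

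**What the plan says.** Section 2.8 fixes the safety population in one sentence: "The safety analysis will be conducted for randomized subjects who have completed at least one study visit and have safety data". The conditions are randomisation, one completed visit and the presence of safety data. In the same paragraph the FAS carries an exposure condition: "all patients will be treated with at least one dose of the study drug", together with a clinical observation.

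Section 2.6.2 states when safety data arise: "Safety assessments are taken on the 1st day (day 1) and the 6th day of the intervention". The caption of Table 3 places the first of these assessments at Visit 1: "On the 1st day, researchers collect the data of medical and treatment history, efficacy observation, safety assessment, and exclusive observation of patients". The table puts randomisation and drug distribution at that same visit. Adverse-event recording is ticked at Visits 2, 3 and 4, not at Visit 1. Under 2.5.1, participants are "advised to take the drugs at home to avoid discussing the drugs".

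Two other sections bear on who stays in the safety set. Section 2.4 excludes a patient whose blind code is exposed, does not say from which analysis, and lists a serious adverse event among the reasons for breaking the blind. Section 2.2.4 treats the data of certain withdrawn patients, including those with an allergic reaction or a serious adverse event, as invalid but keeps them in the FAS. It does not mention the safety set.

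**The concern.** A safety population should contain the people exposed to the product. Here the conditions can be met without exposure, so the safety set can include a patient whom the FAS leaves out for having taken no drug. Such a patient adds to the denominator but cannot have a drug-related event. The likely result is that adverse-event rates, and differences between dose groups and control, are pulled toward no difference. That is the less cautious direction in a dose-finding trial that monitors blood glucose because of a finding in rats (2.6.2).

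The opposite fault is also open. Nothing in 2.8 protects exposed patients from the exclusion in 2.4. If that exclusion reached the safety analysis, patients unblinded because of a serious adverse event would drop out of the analysis meant to count them.

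**Working it through.** The document states no adverse-event rate, no safety-set size and no number of never-dosed patients, so there is no figure of its own to reproduce. The check has two parts.

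**1. Can a never-dosed patient qualify?**

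- Randomised: yes, at Visit 1 (Table 3).
- At least one completed visit: Visit 1 meets this.
- Has safety data: the Day 1 blood, urine, liver, renal, glucose and ECG tests are called safety assessments in 2.6.2 and Table 3.
- Dose taken: not asked for in the safety sentence. The drug is handed out at Visit 1 for use at home, and the article describes no supervised first dose.

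So such a patient can qualify on the wording. No other section adds a dose condition for safety.

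**2. How much would it matter?**

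Inputs:

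- n = 60 per group (2.3; 4 × 60 = 240).
- k = never-dosed patients in a group (assumption).
- r = event rate among dosed patients (assumption).
- b = event rate among never-dosed patients (assumption; b = 0 in the table).

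Formula: reported rate = [r × (60 − k) + b × k] / 60. With b = 0 this is r × (60 − k)/60, a relative understatement of k/60.

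| k | k/60 | r = 5% | r = 10% | r = 20% |
|---|---|---|---|---|
| 0 | 0% | 5.0% | 10.0% | 20.0% |
| 1 | 1.7% | 4.9% | 9.8% | 19.7% |
| 3 | 5.0% | 4.75% | 9.5% | 19.0% |

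Example: 10% × 57/60 = 9.5%.

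If b is above zero, a single arm's rate is diluted less, and if b = r it is not diluted at all. The contrast between arms still shrinks. With the same k and the same b in two arms, the b terms cancel and the reported difference is the true difference × (60 − k)/60. For example, a 5-point difference with k = 3 becomes 5 × 57/60 = 4.75 points.

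**Laboratory results.** Treatment-emergent changes can be seen only at Day 6. Dilution arises only if patients without a Day 6 value are counted in the denominator. Section 2.8 does not say whether they are.

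**The case against.** The strongest reply is that the trial's calendar is itself tied to dosing. Section 2.6.5 sets Day 1 as the first day of medication, and the Table 3 caption counts the later visits from first intake. On that reading a never-dosed patient has no Day 4, 6 or 11. Since adverse events are recorded only from Visit 2, having safety data could also mean having post-treatment data, which would remove anyone who takes the box home and never returns.

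Part of this stands. It would be too strong to say that every randomised patient clearly qualifies before any dose, or that attending a visit is the only condition. But Visit 1 must come before the first dose, its tests carry the safety label, and a definition of study days is not a membership rule. The wording leaves the point open.

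The objection is also right on several stronger readings that a reader might infer:

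- **That the 20% loss allowance in 2.3 measures non-starters.** That would be 12 of 60, and 10% × 48/60 = 8.0%. The allowance is for loss in general, and nothing suggests that it occurs before dosing. Patients are symptomatic, enrolled within 48 hours of onset, given drug at Visit 1 and contacted daily.
- **That the bias differs systematically by arm.** Packages are uniform and allocation is blinded, so non-starting should differ between arms only by chance.
- **That non-starters have no events.** Section 2.7 counts worsening symptoms and concomitant disease as adverse events, and both can occur in an untreated cold.
- **That laboratory rates are necessarily understated.** They are not, if only available Day 6 results are used.

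**Conclusion.** The point holds as a defect in a stated definition. The safety set has no exposure condition, while the FAS beside it does, and a never-dosed patient could enter as worded. The possible effect is dilution of adverse-event comparisons toward no difference.

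Its size is unknown and probably small: a relative understatement of 1.7% with one never-dosed patient among 60 and 5% with three, assuming no events in them, and nil if everyone starts treatment. The documents do not support a claim that the rates will in fact be understated.

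This is a minor point. It is still worth correcting because the rule is fixed in the article, the change costs almost nothing, and the same sentence can settle how the exclusion of unblinded patients in 2.4 relates to the safety analysis.

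**What to change.** Replace the safety sentence in 2.8 with a definition on these lines: the safety set comprises all randomised participants who took at least one dose, analysed by the treatment actually taken, and retained whatever their later withdrawal or unblinding. State that the exclusion in 2.4 and the invalid-data rule in 2.2.4 do not apply to the safety set, so that a patient unblinded for a serious adverse event is still counted.

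For laboratory changes, use participants with a Day 6 value as the denominator and report the number missing in each group.

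The cost is a sentence or two and no new data. Whether a first dose was taken can be judged from the daily contacts and the package count already planned in 2.5.2. The downside is that reported rates may look slightly less favourable.

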**Methods/Design:**

This is a multicenter, randomized, double-blind, placebo-controlled, phase II clinical trial. A total of 240 eligible patients will be recruited from five centers. Patients are randomly assigned to high-dose group, middle-dose group, low-dose group, or control group in a 1 : 1 : 1 : 1 ratio. All drugs are required to be taken 3 times daily for 5 days with a 5-day follow-up period. Primary outcomes are duration of all symptoms, total score reduction on Jackson's scale, and TCM symptoms scale. Secondary outcomes include every single TCM symptom duration and score reduction, TCM main symptoms disappearance rate, curative effects, and comparison between Jackson's scale and TCM symptom scale.

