### 2.4. Randomization and Blinding

According to a stratified block randomization method, the PRCO PLAN function of the analysis system of SAS software (SAS Institute, Inc., Cary, NC, USA) was used to generate the random number grouping table according to the number of cases and the random proportion of the participating units. There are 5 centers and 4 groups (high-dose group, middle-dose group, low-dose group, and control group), and each group is divided into two layers in a 1 : 1 ratio, while one layer is aged between 45 and 60 years and the other layer is aged between 61 and 75 years. So each group in one single center will recruit 12 patients, with 6 patients between 45 and 60 years old and 6 patients between 61 and 75 years old. Eligible patients are randomly allocated to the high-dose group, middle-dose group, low-dose group, or control group in a 1 : 1 : 1 : 1 ratio. The randomization sequence was generated by the Health Statistics Department of the Fourth Military Medical University of China, which is independent of the trial. The details of randomization sequences are unknown to researchers and outcome assessors who participate in the study and kept in two copies in an opaque, sealed, and stapled envelope that will be kept concealed until the end of the outcome assessment.

The blinding codes are preserved and protected separately by West China Hospital and the other four participating centers. Emergency letters are prepared by a statistician in which the random code and group assignment are included. If the blind code is exposed, the corresponding patient will be excluded. Any of the following situations could call for a blind breaking and urgent measure: a serious adverse event, serious complication, or deteriorative condition.

Following the blinding principle, the five participating centers are isolated from the sponsor unit during the study and they will contact only the supervision agency (Beijing Chuangli Medical Technology Development Co., Ltd., China), which is responsible for contacting participating centers and monitoring the progress of research but is blind to group assignment.

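### Section 2.8 assigns Kaplan-Meier and the log-rank test to the Jackson and TCM score reductions, two of the three primary outcomes, although these are numeric differences and not times to an event

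*Protocol article*

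**What the plan says.** The abstract (Methods/Design) names the outcomes: "Primary outcomes are duration of all symptoms, total score reduction on Jackson's scale, and TCM symptoms scale". One is a duration and two are score changes.

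Section 2.6.5 defines the changes. Jackson's scale has eight items scored 0 to 3. They are summed on days 1, 4, 6 and 11, and "the score reduction will be calculated between the 1st day and the days after the intervention". For the TCM scale, "the score reduction is defined as the scores on the 1st day minus the scores after the intervention", at the same later days. Neither definition contains an event, a threshold or a censoring rule. The duration outcome in the same section does have an explicit end point.

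Section 2.8 then puts durations and score changes in one list. It opens with "All symptom durations, total score reductions on Jackson's scale and TCM symptoms, the duration of each TCM symptom" and closes with "the reduction score of TCM symptoms will be estimated with the Kaplan-Meier technique and compared using the stratified log-rank test". The strata of the log-rank test are not named.

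Two further statements in section 2.8 bear on the point. One reads "Comparisons among different dose groups and age layers will be conducted with an analysis of variance (ANOVA" and adds a least significant difference t-test, without saying for which outcome. The other provides for "the Cochran-Mantel-Haenszel test stratified by clinical centers" and a logistic regression whose covariates are not named. According to section 2.4, randomisation is stratified within centres by age: "one layer is aged between 45 and 60 years and the other layer is aged between 61 and 75 years".

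**The concern.** Kaplan-Meier estimates the distribution of a time to an event, and log-rank compares such distributions. A score reduction at a fixed visit is neither a time nor an event. It can be zero, or negative in a patient who worsens.

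The protocol expects such patients. Section 2.2.4 covers those whose symptoms do not improve or worsen after 72 hours on treatment: they can be withdrawn after assessment but stay in the full analysis set, which section 2.8 makes the primary efficacy set.

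The trial is meant to show symptom reduction and to find the optimal dose (sections 1 and 4). Choosing a dose needs an estimated effect for each dose, in points on the scale and with its uncertainty. The method named for two of the three primary outcomes does not supply that.

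**Working it through.** **1. Range of the outcome.** Jackson's scale runs from 0 to 8 x 3 = 24. Entry requires at least 2 points (section 2.2.1). The reduction can therefore lie anywhere from 2 - 24 = -22 to 24 - 0 = 24. Negative values are possible by definition, and a survival time cannot be negative.

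**2. Is there an event to which the method could refer?** A time-to-reduction reading needs a defined amount of reduction. The only threshold in the article is a reduction of at least 50% (section 2.6.6). It belongs to the secondary curative-effect outcome, recorded on day 11, and is not tied to the primary score reductions.

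**3. Censoring.** If the reduction itself is used as the time variable, the horizontal axis is in score points. A patient withdrawn after 72 hours may have no day-6 or day-11 score, and the days on study give no point on that axis at which to censor. The feature that makes Kaplan-Meier useful for durations is absent.

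**4. What the test does if run anyway.** The only sample-size figure available is 50 evaluable per group at 90% power and two-sided 0.05 (section 2.3). The article gives no effect size, SD or endpoint behind the 50, so it cannot be re-derived. The effect below is solved from it:

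- d = (1.960 + 1.282) x sqrt(2/50) = 3.242 x 0.2 = 0.648 SD.

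The simulation used 20,000 trials of two arms with 50 each. Reductions were normal, untied, unstratified and uncensored.

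| True difference | t-test | Log-rank on the reduction | Log-rank with sign reversed |
|---|---|---|---|
| 0 | 0.049 | 0.053 | 0.052 |
| 0.648 SD | 0.895 | 0.837 | 0.832 |

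The false-positive rate stays near 5%. Power falls by about 6 percentage points (0.895 - 0.837 = 0.058; 0.895 - 0.832 = 0.063).

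**5. What the fix would add.** With equal variance s^2 at both visits and correlation r between baseline and follow-up:

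- Unadjusted change: variance 2(1 - r)s^2.
- ANCOVA: variance (1 - r^2)s^2.
- Ratio: (1 - r^2) / [2(1 - r)] = (1 + r)/2.

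This gives 0.65 at r = 0.3, 0.75 at r = 0.5 and 0.85 at r = 0.7. The article gives no r. Equal variance is also an assumption. With different SDs s0 (day 1) and s1 (later), the two variances differ by (s0 - r s1)^2, which is never negative, so adjustment does not lose precision in this comparison. This is a gain from the fix. It does not measure the error in section 2.8.

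**The case against.** The strongest defence is that the procedure still works as a test. Without censoring, the Kaplan-Meier curve is one minus the empirical distribution, and log-rank is a rank test that does not change when a constant is added. Negative values can be ranked. This stands: the simulation shows the type I error kept and a moderate loss of power. A reader might infer that the primary inference would be invalid or that no effect could be interpreted, and the evidence does not support that.

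Three other inferences also go too far.

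- **The ANOVA is a competing analysis that ignores baseline.** Section 2.8 names no outcome for the ANOVA and does not call it an alternative; it may describe only pairwise comparisons of doses and age layers. A change score already subtracts the day-1 value. At most, the day-1 score is not named as a covariate, which a fuller document may settle.
- **Age is left out of the analysis.** Only the CMH test is limited to centre in the text, and that test suits categorical outcomes. Age layers appear in the ANOVA sentence and may be among the unnamed log-rank strata or logistic covariates.
- **The rate of main symptoms is the same error.** The disappearance of a symptom is an event, and patients are contacted daily (section 2.5.2), so Kaplan-Meier could give the proportion resolved by a given day. The wording is loose, because section 2.6.6 defines a percentage on days 4 and 6, but the fault is milder.

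None of this removes the core. The method is assigned to the two score reductions by name, so it is a statement to correct and not a detail left to the analysis plan.

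**Conclusion.** Wrong as written, for two of the three primary outcomes. The harm is an unsuitable method: no mean difference per dose in scale points, no way to censor withdrawn patients, and lower power.

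The power figure of about 0.83 to 0.84 against 0.90 is illustrative. It rests on normal, untied data in two arms of 50 and on an effect solved from the stated 90% power. Integer scores with ties, a stratified test or another effect size would change it. The precision gain from baseline adjustment depends on an assumed correlation and should not be quoted as the size of this error.

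**What to change.** Reword section 2.8, and the analysis plan to match, before unblinding:

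- Restrict Kaplan-Meier and the stratified log-rank test to the duration outcomes, and name the strata.
- Analyse the Jackson and TCM total scores by ANCOVA, or by a repeated-measures model over days 4, 6 and 11, with treatment, day-1 score, centre and age layer (45-60, 61-75). Report the adjusted mean difference from control for each dose with its confidence interval.
- State which outcomes the ANOVA sentence covers, or remove it.

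Two secondary improvements cost nothing: stratify the CMH test by age layer as well as centre, and analyse the disappearance rate on days 4 and 6 as a proportion.

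No new data are needed. The day-1 score, centre and age layer are already collected, and the planned 240 patients do not change.
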